#### 2.7.2. Secondary Outcomes

Secondary outcomes will include the functional ability of oral intake and the quality of life related to dysphagia.

The Functional Oral Intake Scale (FOIS) is used to measure a patient’s level of eating ability. The scale ranges from 1 (no ability to swallow) to 7 (normal swallowing). Scores from 1 to 3 correspond to non-oral feeding or requiring additional tube feeding, while scores from 4 to 7 correspond to an oral diet, considering special modifications and compensations at certain levels. The FOIS is a valid and reliable scale for stroke patients [46].

The quality of life of patients with dysphagia will be assessed using the Swallowing Quality of Life questionnaire (SWAL-QOL) [47]. This tool is composed of 44 items divided into 11 subscales. The assessment items include burden, food selection, eating loss, eating duration, eating desire, fear, sleep, fatigue, communication, mental health, and social functioning. Each item is scored according to a Likert scale ranging from 1 (worst condition) to 5 (best condition). Lower scores are associated with poorer quality of life. SWAL-QOL is a valid and reliable scale for patients with dysphagia.

### 2.8. Sample Size Calculation

The sample size was calculated using G*Power software, version 3.1.9.2. Based on a previous study, our control group’s expected post-treatment PAS score is 4.62 ± 0.77 [48]. According to a power calculation of 80% and assuming a clinically relevant difference of one point on the PAS score between the study groups, with a standard deviation of 1.2 [49], we determined a total sample size of 55 participants. The calculation is based on an alpha level of 95%, accounting for a 15% dropout rate.

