### 2.9. Statistical Analysis

Data will be analyzed using the Statistical Package for the Social Sciences (SPSS) for Windows (version 26, IBM, Armonk, NY, USA). Categorical data will be reported as frequencies and percentages, while continuous variables will be summarized using means and standard deviations. The Shapiro–Wilk test will be used to assess data normality. Differences between groups will be examined with the Chi-square test for categorical variables. For continuous variables, Student’s t-test will be applied for normally distributed data, and the Mann–Whitney U test will be used for non-parametric data. Effect sizes will be calculated using Cohen’s d, with the following values: a small effect is indicated by 0.3, a moderate effect is indicated by 0.5, and a large effect is indicated by 0.8.

Statistical significance will be determined at *p* < 0.05. Participants with adherence rates of 80% or less, based on home diaries and attendance to standard speech and language sessions, will be excluded from the statistical analysis.

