A study conducted by Krekeler et al. [17] observed that the dosage and intensity in clinical practice are lower compared to research studies. In our study, the respiratory muscle training devices are relatively inexpensive, portable, and easy to use. They require no specialist assistance, making them suitable for use in a home environment. A previous trial focused on supervised, home-based respiratory muscle training showed positive results, achieving a significant improvement in the quality of life of the participants [56]. Our study seeks to increase accessibility to therapy and improve the benefits of the standard intervention by increasing the dosage. Treatment adherence is an important but still unresolved health issue, especially in interventions involving home-based exercises [57]. Increased compliance is linked to an increase in cost-effectiveness. Several systematic reviews have reported that diaries are one of the most used tools to measure adherence in home-based approaches [58,59]. In our study, the patients will complete a diary indicating the repetitions and the symptoms associated with exercise performance.

The proposed home-based respiratory training ensures an individualized program with the appropriate intensity and duration, adapted to the symptoms and baseline values of each participant. Adherence will be facilitated through regular monitoring and program adjustments based on patient progress and feedback. Additionally, the home-based respiratory training will be integrated with other therapeutic interventions for dysphagia, such as dietary modifications, postural adjustments, and traditional swallowing exercises, to achieve comprehensive rehabilitation.

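### The sample size of 55 allows for 15% dropout but makes no stated allowance for the adherence exclusion in section 2.9, so the stated 80% power holds only while total loss stays at or below about 15%

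*Protocol article*

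**What the plan says.** Section 2.8 sizes the trial on the Penetration–Aspiration Scale (PAS), "assuming a clinically relevant difference of one point on the PAS score between the study groups", "with a standard deviation of 1.2", at 80% power. It concludes: "we determined a total sample size of 55 participants. The calculation is based on an alpha level of 95%, accounting for a 15% dropout rate". Dropout is the only loss it names.

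Section 2.9 fixes a further loss. Adherence is judged from the home diaries and from attendance at the standard speech and language sessions, and anyone at 80% or less "will be excluded from the statistical analysis". The article gives no expected rate for these exclusions and describes no analysis that keeps the excluded participants.

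On how common poor adherence may be, the Discussion (section 4) remarks: "Treatment adherence is an important but still unresolved health issue, especially in interventions involving home-based exercises". Against that, section 2.6.1 provides a weekly video call to review the diary, section 3 expects the home-based format to help adherence, and section 4 says monitoring and programme adjustment will support it. None of these places gives a rate.

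**The concern.** The number analysed is the number randomised, less dropouts, less completers excluded for adherence. Section 2.8 counts the first loss and is silent on the second, although the second is a fixed rule of the plan. Power is a property of the set that is analysed, so the 80% was derived for a larger set than section 2.9 may leave.

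The rule is easy to meet. Section 2.6.2 schedules 3 × 6 = 18 therapy sessions. If attendance is judged on its own, missing four gives 14/18 = 77.8%, and a participant in either arm who finished the trial is removed. Section 2.6.1 schedules 2 × 5 × 6 = 60 home sessions. If adherence is counted by session, 48/60 is exactly 80%, which the rule also excludes.

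PAS is the outcome on which the trial is sized. If losses exceed the allowance, a null PAS result would look like stronger evidence against a one-point difference than it is.

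**Working it through.** **Inputs.** From section 2.8: difference 1 point, SD 1.2, power 80%, dropout 15%, total 55. From section 2.5: 1:1 allocation. From section 2.9: significance at 0.05 and, for normally distributed data, the t-test. The alpha of 95% in section 2.8 is read as 5%. Sidedness is not stated; two-sided reproduces 55, while one-sided gives 43 to 45. The control-group SD of 0.77, also quoted in section 2.8, does not reproduce 55 either (it gives 24 to 26).

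**Step 1: reproduce 55.** By the normal approximation, n per arm = 2(z₀.₉₇₅ + z₀.₈₀)² SD²/Δ² = 2 × (1.960 + 0.842)² × 1.44 / 1 = 22.6, so 23 per arm and 46 in total. Then 46/0.85 = 54.1, rounded up to 55. This matches exactly, with dropout as the only inflation. The exact t-test needs 24 per arm, 48 in total, and 48/0.85 = 56.5, so 57. That is within two participants of the stated figure.

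**Step 2: margin left after 15% dropout.** 55 × 0.85 = 46.75, against 46 (normal) or 48 (t-test) needed. With n = 23.375 per arm and d = 1/1.2 = 0.833, the noncentrality is d√(n/2) = 0.833 × √11.69 = 2.85 on 44.75 degrees of freedom. Power is 79.6% by the t-test and 81.3% by the normal approximation. Nothing is left over for a second loss.

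**Step 3: add adherence exclusions.** Let x be the share of completers excluded, equal in both arms, on top of 15% dropout. The values of x are assumptions. The number analysed is 55 × 0.85 × (1 − x).

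| x | Analysed | Total loss, 1 − 0.85(1 − x) | Power, t-test | Power, normal |
|---|---|---|---|---|
| 0% | 46.8 | 15.0% | 79.6% | 81.3% |
| 5% | 44.4 | 19.3% | 77.4% | 79.3% |
| 10% | 42.1 | 23.5% | 75.1% | 77.1% |
| 20% | 37.4 | 32.0% | 69.8% | 72.2% |
| 30% | 32.7 | 40.5% | 63.6% | 66.4% |

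If exclusions fall only in the experimental arm, the t-test power is 77.3% at 10%, 74.6% at 20% and 71.2% at 30%.

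**Step 4: express it as total loss.** What matters is the sum of the losses, whatever their cause.

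| Total loss from 55 | Analysed | Power, t-test |
|---|---|---|
| 10% | 49.5 | 81.9% |
| 15% | 46.8 | 79.6% |
| 20% | 44.0 | 77.0% |
| 25% | 41.2 | 74.2% |
| 30% | 38.5 | 71.1% |

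So 5% dropout with 5% of completers excluded (total 1 − 0.95 × 0.95 = 9.75%) gives 82.0%, and 10% dropout with 5% excluded (total 14.5%) gives 79.8%. Both keep the stated power in round figures.

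**The case against.** A reader might infer that the trial does not have its stated 80% power, or that any adherence exclusion costs it. The documents support neither. The article gives no non-adherence rate, so every shortfall in step 3 rests on an assumed one. The 15% is a planning allowance and may not be used up; as step 4 shows, some completers can be excluded with power still at about 80% if dropout is lower. This objection stands, and it is why the point is framed in terms of total loss.

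Dropout is also undefined in section 2.8 and might have been meant to cover everyone lost to the analysis, in which case only the label is unclear. That is possible, and a condensed article may leave the definition to the full protocol. On the ordinary meaning, however, a dropout leaves the trial, whereas section 2.9 describes people identified from diaries and attendance records and removed at analysis. The two should be connected in words.

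Nor is 55 a miscalculation: it reproduces from the stated inputs. The remark on adherence in section 4 is general, and the weekly calls and monitoring may keep exclusions low. It does not establish a rate of 20% or 30%.

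Finally, the effect in an adherent subset may differ from one point. After 15% dropout, 80% power would need a difference of about 1.06 points with 10% of completers excluded, or about 1.13 with 20%. A larger effect among adherers could thus offset the loss, but section 2.8 assumes one point between the study groups and makes no such adjustment.

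**Conclusion.** The point holds in conditional form. The 80% power was derived without a stated allowance for a loss that the plan's own rule imposes, and the dropout allowance has no slack to absorb it. Power is about 80% while total loss is at or below about 15%, and lower beyond that: about 77%, 75% or 70% if 15% drop out and 5%, 10% or 20% of completers are then excluded.

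This rests on a one-point difference, SD 1.2, a two-sided 5% t-test, exclusions equal across arms, an effect unchanged by the exclusions, and dropout not already including them. The actual size of any shortfall cannot be known from the article. The correction is worth making because the sample size section states a power on which readers of the PAS result will rely.

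**What to change.** Keep N = 55. In section 2.8, state that 80% power applies to a total loss of about 15% from all causes, dropout and adherence exclusions together, and give the power at larger total losses: about 77% at 20%, 74% at 25% and 71% at 30%. If the 15% was meant to include the adherence exclusions, call it total loss to analysis instead of dropout. In section 2.9, refer back to that allowance.

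Alternatively, make the main analysis include all randomised participants with outcome data, whatever their adherence. That removes the mismatch at its source and also avoids selecting participants after randomisation.

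The first option costs only wording in sections 2.8 and 2.9; the stated power becomes conditional and less favourable. The second changes the analysis set but needs no further participants. Restoring 80% power by recruitment would be the expensive route: 48/(0.85 × 0.90) = 62.7, so 63 participants at 10% exclusion, or 48/(0.85 × 0.80) = 70.6, so 71 at 20%. The point does not require it.

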### 2.5. Randomization

Participants in this study will be randomly assigned (1:1 ratio) to either an experimental or a control group. The eligibility of participants will be assessed by an independent researcher not involved in the randomization process. The randomization will be performed by a researcher not involved in the study procedure. The randomization sequence will be generated by a computer program (https://www.randomizer.org). The assessment will be carried out by a therapist blinded to the treatment assignments.

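### The sample-size statement gives alpha as 95% where only a two-sided 5% fits its total of 55; the 55 itself stands to within about one power point, before any adherence exclusions

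*Protocol article*

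**What the plan says.** Section 2.8 (Sample Size Calculation) names G*Power and gives these inputs: 80% power, "assuming a clinically relevant difference of one point on the PAS score between the study groups", and a standard deviation of 1.2. From these, "we determined a total sample size of 55 participants". The section ends: "The calculation is based on an alpha level of 95%, accounting for a 15% dropout rate". It does not give the sidedness of the test, the number needed before dropout, or how the dropout allowance was applied.

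Section 2.9 (Statistical Analysis) sets the threshold: "Statistical significance will be determined at *p* < 0.05". For continuous outcomes, "Student’s t-test will be applied for normally distributed data, and the Mann–Whitney U test will be used for non-parametric data". It then excludes from the analysis anyone whose adherence is 80% or less, judged from home diaries and from attendance at the standard therapy sessions. Section 2.5 (Randomization) sets 1:1 allocation.

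**The concern.** Alpha is the type I error rate, and no trial is designed to accept 95%. The figure is a confidence level placed under the wrong name, and it disagrees with the threshold in section 2.9. It stands in the trial's only sample-size justification, so a reader who wants to check the 55 must first guess the alpha and the sidedness. The guess matters: on the same inputs, a one-sided 5% t-test needs 19 per arm and a two-sided one needs 24.

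Two further questions follow. One is whether 55 delivers 80% power after the stated 15% loss. The other is whether that 15% is the only loss to expect, given that section 2.9 removes participants for low adherence as well.

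**Working it through.** **Inputs.** Difference 1 PAS point, SD 1.2, power 80%, dropout 15%, total 55 (section 2.8); 1:1 allocation (section 2.5); alpha 0.05 (section 2.9). Sidedness is not stated, so both are tried. Standardised difference: d = 1/1.2 = 0.833.

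**Reproducing the 55: normal approximation, two-sided 5%.**
- n per arm = 2 × (1.960 + 0.842)² × 1.2² / 1² = 22.6, so 23; total 46.
- 46/0.85 = 54.1, rounded up to **55**. This is the stated figure.

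**The t-test calculation (noncentral t), two-sided 5%.**
- The smallest equal arms reaching 80% are 24 (power 80.7%); total 48.
- 48/0.85 = 56.5, rounded up to 57. The stated 55 is 2 fewer.
- Multiplying instead, 48 × 1.15 = 55.2, also lands near 55. The article does not show which route was taken.

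**One-sided 5%.**
- Normal approximation: 2 × (1.645 + 0.842)² × 1.44 = 17.8, so 18 per arm; 36/0.85 = 42.4, so 43.
- t-test: 19 per arm; 38/0.85 = 44.7, so 45.
- Neither gives 55.

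**Other readings.**
- Alpha taken literally as 0.95 in the same formula gives 3 per arm, so the 95% was not what the calculation used.
- The control-group SD of 0.77, also quoted in section 2.8, gives 11 per arm by two-sided t-test; 22/0.85 = 25.9, so 26. The SD behind the 55 is therefore 1.2.

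**Power that 55 leaves after 15% dropout.** 55 × 0.85 = 46.75, so 46 or 47 participants.

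| Analysed | Arms | Power, two-sided 5% t-test |
|---|---|---|
| 48 | 24/24 | 80.7% |
| 47 | 23/24 | 79.8% |
| 46 | 23/23 | 78.9% |

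The gap to 80% is 0.2 to 1.1 points. By the normal approximation, 46 analysed gives 80.7% and there is no gap.

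**If adherence exclusions come on top of the 15%.** The article gives no expected rate, so the shares below are assumptions.

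| Assumed further loss from 46.75 | Analysed | Power, two-sided 5% t-test |
|---|---|---|
| 5% | 44 | 77.0% |
| 10% | 42 | 75.0% |
| 15% | 40 | 72.9% |

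**The case against.** The best defence is that the slip is harmless. Section 2.9 states the operative threshold, 95% is easily recognised as the confidence level, and the 55 shows that 5% two-sided was used. A condensed article may also leave sidedness to the full plan. All of this is fair as to consequence: neither the design nor the test changes. It does not make the sentence right, because the figure is stated wrongly rather than left out.

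A reader might go further and infer that 55 is a miscalculation, obtained by multiplying 48 by 1.15 instead of dividing by 0.85, and that 57 or 58 must be enrolled. The documents do not support that. The normal approximation with the correct division gives exactly 55. G*Power and the planned Student's t-test make the t-test route plausible, but the article names neither the test behind the calculation nor the number before dropout. Even on that route the shortfall is about one power point at most, on inputs that are themselves planning guesses.

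Nor does the odd total count against the plan. It splits 28/27 with practically no loss of power, and section 2.5 fixes a ratio, not equal arms.

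On adherence, the defence is that dropout is not defined, so the 15% might already cover those exclusions. That stands as a possibility. For this reason the lower power figures are conditional, and no single one of them can be put forward as the trial's power.

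**Conclusion.** The alpha of 95% is an error as written and contradicts section 2.9; of the 5% readings tried, only the two-sided one yields 55. It is an error of wording with no effect on the calculation.

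The 55 holds on the plan's own inputs: exact by the normal approximation, 2 short by the t-test, with 78.9% to 79.8% power once 15% are lost. The trial is not materially underpowered by dropout alone.

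What remains open is that section 2.8 budgets only for dropout while section 2.9 also removes participants for low adherence. At 55 there is no spare margin on the t-test route, so any exclusions beyond the 15% lower the power, to about 77% to 73% over the assumed range of 44 to 40 analysed. All power figures rest on a true difference of one point, SD 1.2 and a two-sided 5% t-test; the adherence losses are assumptions without a source in the article.

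**What to change.** Replace the last sentence of section 2.8 with a statement along these lines: two-sided alpha of 5%, difference of 1 point, SD 1.2; 55 enrolled with 15% dropout leaves 46 to 47 evaluable participants, which gives about 79% to 80% power by t-test.

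Then do one of the following:
- State that the 15% does not name the adherence exclusions in section 2.9 and that power falls further if they come on top, with a short range such as the one shown above.
- Base the power statement on all randomised participants, whatever their adherence, and make section 2.9 describe the analysis that this power refers to.

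The cost is one or two sentences, with the power given as about 79% to 80% instead of a flat 80%. The second option also means aligning the analysis population in section 2.9. No additional enrolment is needed.

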### 2.9. Statistical Analysis

Data will be analyzed using the Statistical Package for the Social Sciences (SPSS) for Windows (version 26, IBM, Armonk, NY, USA). Categorical data will be reported as frequencies and percentages, while continuous variables will be summarized using means and standard deviations. The Shapiro–Wilk test will be used to assess data normality. Differences between groups will be examined with the Chi-square test for categorical variables. For continuous variables, Student’s t-test will be applied for normally distributed data, and the Mann–Whitney U test will be used for non-parametric data. Effect sizes will be calculated using Cohen’s d, with the following values: a small effect is indicated by 0.3, a moderate effect is indicated by 0.5, and a large effect is indicated by 0.8.

Statistical significance will be determined at *p* < 0.05. Participants with adherence rates of 80% or less, based on home diaries and attendance to standard speech and language sessions, will be excluded from the statistical analysis.

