#### 2.7.1. Main Outcomes

The main outcomes will include the aspiration risk, the strength of respiratory muscles, and peak cough flow. 

The penetration or aspiration risk will be assessed using the Penetration–Aspiration Scale (PAS) [39]. The PAS is a valid and reliable 8-point scale used during videofluoroscopy assessment. It evaluates the depth of airway invasion, the material remaining after swallowing, and the patient’s response to aspiration. The scores range from 1 (material does not enter the airway) to 8 (material enters the airway, passes below the level of the vocal folds, and no effort is made to eject it). The assessment will be conducted by two experienced researchers, who are blinded to the swallowing performance before and/or after the targeted swallow task. This scale has been reported to be a valid tool for differentiating between normal and abnormal airway protection [39]. 

Respiratory muscle strength will be evaluated using maximal inspiratory pressure (MIP) and maximal expiratory pressure (MEP) measurements [40]. The patients will be evaluated in a sitting position while wearing a nose clip. To evaluate the MIP, the patients will be instructed to exhale air near the residual volume and then inhale through the mouthpiece. To measure MEP, the patients will be asked to inhale air near total lung capacity and then exhale the air through the mouthpiece. Three maneuvers will be performed, ensuring no more than a 20% difference among them [41]. The cut-off values to determine muscle weakness are 62 and 83 cmH_2_O for MIP in females and males, respectively, and 81 and 109 cmH_2_O for MEP in females and males, respectively [42].

Voluntary peak cough flow (L/min) will be evaluated using a peak flow meter (Micro Medical, Cambridge, UK) [43]. This parameter assesses the maximum expiratory flow during a cough to evaluate the efficacy of secretion clearance. The patient will be seated in a chair, will inhale as much air as possible, and then cough as forcefully as possible through the mouthpiece. The maneuver will be performed three times, and the mean of the values will be included in the analysis. Standardized values in healthy adults range between 360 and 400 L/min [44]. An effective cough is associated with having a peak flow rate of over 160 L/min, while a rate below 270 L/min is associated with increased secretion retention and a higher risk of infection [45].

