## 3. Results

The expected outcomes include improved swallowing function. Patients are supposed to improve swallowing safety and efficiency. The addition of respiratory training to standard intervention is expected to improve coordination between breathing and swallowing, thereby reducing the risk of aspiration and facilitating better management of various food textures. A reduction in the frequency and severity of aspiration events is expected, leading to improved airway protection and a lower incidence of aspiration pneumonia. The respiratory training program is designed to strengthen both inspiratory and expiratory muscles. As a result, significant gains in respiratory muscle strength are expected, as evidenced by increased MIP and MEP values. Patients are also expected to achieve a more effective cough, which is relevant for clearing the airway and reducing the risk of aspiration pneumonia. This improvement should be reflected in higher peak cough flow measurements. Enhancements in swallowing ability are likely to contribute to a better quality of life, including reduced symptoms related to dysphagia and increased comfort during eating and drinking.

The home-based format of the program is expected to improve adherence, promote consistent participation, and achieve better long-term results. By integrating respiratory training with standard therapeutic interventions, the program aims to address both swallowing and respiratory issues more effectively, leading to improved overall rehabilitation outcomes.

The authors will present the study results in a peer-reviewed journal. The procedures and patient involvement at various stages of the study will be illustrated in a flow diagram. The article will highlight the main findings, starting with a table that details the descriptive characteristics of the sample. This will be followed by data comparing baseline outcomes between groups for both primary and secondary measures. Finally, the results of the intervention outcomes will be presented, including within-group and between-group changes, with effect sizes calculated using Cohen’s d.

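### A normality pre-test chooses the analysis of the 8-point PAS, so the estimand is not fixed in advance and Cohen's d will often sit beside a rank test

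*Protocol article*

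**What the plan says.** Four parts of the protocol article bear on this.

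- **Section 2.7.1 (Main Outcomes)** lists aspiration risk first and measures it by PAS: "The PAS is a valid and reliable 8-point scale used during videofluoroscopy assessment". Scores are whole numbers from 1 to 8. Two researchers carry out the rating; how their scores are combined is not described.
- **Section 2.8 (Sample Size Calculation)** plans on PAS as a mean, "assuming a clinically relevant difference of one point on the PAS score between the study groups", "with a standard deviation of 1.2", and arrives at 55 participants with 15% dropout. It also gives an expected control value of 4.62 with SD 0.77. The software is named but the test is not.
- **Section 2.9 (Statistical Analysis)** sets the rule: "The Shapiro–Wilk test will be used to assess data normality", after which Student's "t-test will be applied for normally distributed data, and the Mann–Whitney U test will be used for non-parametric data". It does not say whether normality is checked per arm, pooled or on residuals. It then adds "Effect sizes will be calculated using Cohen’s d", whichever test was used.
- **Section 3 (Results)** repeats that within-group and between-group changes will be shown "with effect sizes calculated using Cohen’s d". No rank-based effect measure appears anywhere.

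Table 1 shows PAS measured before and after the intervention.

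**The concern.** PAS can take only eight values, and with an SD near 1.2 only five or six of them occur in a typical arm. Shapiro–Wilk reacts to the resulting ties even when the underlying severity is normal. For this outcome the pre-test therefore largely detects the scale and says little about the shape of the distribution.

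Three things follow.

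1. Whether the main comparison concerns mean PAS or rank order is decided by the trial's own data.
2. On the rank route, the p-value comes from Mann–Whitney while the reported effect is a standardised mean difference. The reader gets no estimate that belongs to the test.
3. The planning figure is a difference in means, which matches only the less likely branch.

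In addition, neither named test adjusts for the baseline PAS that the trial collects.

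**Working it through.** **Inputs from the article.** Difference 1 point, SD 1.2, power 80%, dropout 15%, total 55, control 4.62 ± 0.77 (section 2.8); significance at 0.05 (section 2.9); 1:1 allocation (section 2.5). Two-sided testing is assumed because it reproduces the stated total; one-sided variants give 42–45.

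**Step 1: the plan's own figure.** Two-means formula: n per arm = 2(1.960 + 0.842)² × 1.2² / 1² = 22.6, so 23 per arm and 46 in total. Dropout: 46 / 0.85 = 54.1, rounded up to 55. This matches exactly. The noncentral t version needs 24 per arm (48 in total; 48 / 0.85 = 56.5, 48 × 1.15 = 55.2), which is within two patients. The figure therefore behaves like a comparison of means, although the article does not name the test.

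**Step 2: how often the pre-test rejects.** Simulated PAS is a normal score rounded to integers and clipped to 1–8, with means 4.62 and 3.62, a 5% Shapiro–Wilk test, and at least 3,000 trials per scenario.

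| Scenario | Rejects in at least one arm | Rejects on pooled data |
|---|---|---|
| Unrounded normal, SD 1.2, 23 per arm | 10% | 5% |
| Integer, SD 1.2, 20 per arm | 76% | 83% |
| Integer, SD 1.2, 23 per arm | 82–83% | 93–94% |
| Integer, SD 1.2, 24 per arm | 86% | 96% |
| Integer, SD 0.77, 24 per arm | 100% | 100% |
| Integer, SD 1.6–2.0 (assumed), 24 per arm | 51–53% | 73–84% |
| Half-points, SD 1.2, 24 per arm (two ratings averaged, assumed) | 22% | 14% |

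The first and third rows differ only in rounding. The jump from 10% to over 80% is therefore due to ties.

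**Step 3: what the rule does to error rates.** Integer scores, SD 1.2:

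| Per arm | t-test | Mann–Whitney | Two-stage rule |
|---|---|---|---|
| 23 | 0.76 | 0.74–0.75 | 0.74–0.75 |
| 24 | 0.78–0.79 | 0.76–0.77 | 0.76–0.78 |
| 24, SD of the rounded score held at 1.2 | 0.80 | 0.78 | 0.78–0.79 |

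The rule costs 1–2 points against the t-test in every row. Its type I error was 0.043–0.055 across the null scenarios. At SD 1.2 the t-test and Mann–Whitney disagree on significance in 4–5% of trials.

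**Step 4: what baseline adjustment would add.** The baseline–outcome correlation ρ is not in the article, so it is assumed. Covariate adjustment reduces the SD to 1.2 × √(1 − ρ²). For a continuous score with 24 per arm:

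| ρ | Adjusted SD | 1 / SD | Power |
|---|---|---|---|
| 0 | 1.200 | 0.833 | 0.81 |
| 0.3 | 1.145 | 0.874 | 0.84 |
| 0.5 | 1.039 | 0.962 | 0.90 |
| 0.7 | 0.857 | 1.167 | 0.98 |

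A small simulation with rounded scores at ρ = 0.5 gave about 0.87, against 0.76–0.78 unadjusted. Testing change scores instead, which section 3 may intend, gives an SD of 1.2 × √(2(1 − ρ)). At ρ = 0.5 that is 1.2 again, so nothing is gained.

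**The case against.** The strongest reply is that the rule is harmless and written in advance. Type I error is preserved, the two tests rarely disagree, and when the pre-test rejects it sends an ordinal scale to a rank test, which is defensible. Cohen's d beside a rank test is a reporting mismatch and does not alter the p-value. All of this stands, and it limits the size of the point.

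A second reply is that frequent rejection depends on details the article does not settle. This also stands. Averaging two raters would bring rejection down to 22%, an SD of 1.6–2.0 would bring it to about half with per-arm testing, and how the pre-test is applied is not stated. A strict reader could even place PAS among the categorical variables tested by Chi-square. These possibilities weaken the word "usually". They do not rescue the rule, because in each of them the form of the main analysis still depends on something other than the question being asked.

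A third reply is that a fuller analysis plan may name a PAS model. It may, but the article does more than stay silent: it states a selection rule that covers PAS.

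A reader might infer from simulated power near 75% that the pre-test takes the trial down from its stated 80%. The figures do not support that. At 23 per arm the t-test alone reaches only 0.76. The remaining gap comes from rounding, which adds 1/12 to the variance (√(1.44 + 0.083) = 1.23), and from using 23 rather than 24 per arm.

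**Conclusion.** The point holds as a problem of estimand and reporting. Validity is not affected, and the loss of power attributable to the pre-test is small, about 1–2 points. If PAS is analysed as a single integer at the documented SDs with about 23–24 evaluable patients per arm, the pre-test rejects in about 80–100% of trials and the main result is usually a rank test paired with Cohen's d. Under wider assumed SDs with per-arm testing, the choice of test is close to even. The link between the sample size and a comparison of means is inferred from exact reproduction of 55; the article does not name the test. The gain from baseline adjustment depends on a correlation that is assumed, and it disappears at ρ = 0. The change is worth making before the data are seen, with moderate confidence as to its practical effect.

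**What to change.** Delete the normality pre-test and name one baseline-adjusted analysis of PAS with an effect measure that belongs to it. Either of these would do:

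- a proportional-odds model of post-intervention PAS on arm and baseline PAS, reporting the common odds ratio with 95% CI; or
- a linear model (ANCOVA) of post-intervention PAS on arm and baseline PAS, reporting the adjusted mean difference with 95% CI, kept whatever Shapiro–Wilk would show. This option matches the planning figure most closely.

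State how the two raters' PAS scores become one value per patient. Use baseline-adjusted linear models for MIP, MEP and peak cough flow, and limit Cohen's d to outcomes analysed by means. FOIS, a 1–7 scale, falls under the same rule and needs the same treatment as PAS.

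**Cost.** Analysis wording only; Table 1 already schedules the baseline measurements, so no visits or patients are added. An odds ratio is less familiar to readers than a mean difference, and the proportional-odds assumption is hard to check with about 24 per arm and sparse categories. The linear model avoids both drawbacks but treats PAS steps as equally spaced.
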